## Abstract

**Background:**

Coronary heart disease (CHD) and depression are leading causes of disease burden globally and the two often co-exist. Depression is common after Myocardial Infarction (MI) and it has been estimated that 15-35% of patients experience depressive symptoms. Co-morbid depression can impair health related quality of life (HRQOL), decrease medication adherence and appropriate utilisation of health services, lead to increased morbidity and suicide risk, and is associated with poorer CHD risk factor profiles and reduced survival. We aim to determine the feasibility of conducting a randomised, multi-centre trial designed to compare a tele-health program (MoodCare) for depression and CHD secondary prevention, with Usual Care (UC).

**Methods:**

Over 1600 patients admitted after index admission for Acute Coronary Syndrome (ACS) are being screened for depression at six metropolitan hospitals in the Australian states of Victoria and Queensland. Consenting participants are then contacted at two weeks post-discharge for baseline assessment. One hundred eligible participants are to be randomised to an intervention or a usual medical care control group (50 per group). The intervention consists of up to 10 × 30-40 minute structured telephone sessions, delivered by registered psychologists, commencing within two weeks of baseline screening. The intervention focuses on depression management, lifestyle factors (physical activity, healthy eating, smoking cessation, alcohol intake), medication adherence and managing co-morbidities. Data collection occurs at baseline (Time 1), 6 months (post-intervention) (Time 2), 12 months (Time 3) and 24 months follow-up for longer term effects (Time 4). We are comparing depression (Cardiac Depression Scale [CDS]) and HRQOL (Short Form-12 [SF-12]) scores between treatment and UC groups, assessing the feasibility of the program through patient acceptability and exploring long term maintenance effects. A cost-effectiveness analysis of the costs and outcomes for patients in the intervention and control groups is being conducted from the perspective of health care costs to the government.

**Discussion:**

This manuscript presents the protocol for a randomised, multi-centre trial to evaluate the feasibility of a tele-based depression management and CHD secondary prevention program for ACS patients. The results of this trial will provide valuable new information about potential psychological and wellbeing benefits, cost-effectiveness and acceptability of an innovative tele-based depression management and secondary prevention program for CHD patients experiencing depression.

**Trial Registration Number:**

Australia and New Zealand Clinical Trials Register (ANZCTR): ACTRN12609000386235

## Background

Coronary Heart Disease (CHD) and depression are currently two of the most important causes of disability in high-income countries [1] and it is projected that the same will apply to low and middle income countries by 2030 [2]. These conditions often co-exist with approximately 15% of Myocardial Infarction (MI) patients experiencing major depressive disorder (MDD) and another 15-20% exhibiting mild to moderate depression [3]. Patients with post-MI depression are more likely to report impaired health related quality of life (HRQOL) [4], poorer medication adherence [5] and utilisation of health services [6], increased morbidity and suicide risk [7], and poorer CHD risk factor profiles, work outcomes [8] and survival [9]. In particular, depression results in poor uptake and completion of CHD secondary prevention or cardiac rehabilitation programs [10], which have been shown to play a pivotal role in improving CHD risk factor profiles and other clinical outcomes. Indeed, compared with non-depressed patients, depressed patients are three times less likely to be compliant with medical treatment recommendations [11]. The clinical benefits of CHD secondary prevention programs are well documented and include decreased risk of fatal and non-fatal recurrent MI and CVD [12], improved HRQOL, and lower rates of rehospitalisation [13,14]. However, despite the high prevalence of depression following a diagnosis of CHD and the poor outcomes associated with the group [9], it remains poorly recognised and managed in CHD patients.

Traditionally, CHD secondary prevention programs are delivered face-to-face in clinic- or hospital-based settings; however, they suffer from low participation rates due to a range of barriers including poor accessibility and access [15]. Symptoms of depression following Acute Coronary Syndrome (ACS) - including hopelessness, helplessness, and apathy - can further impede participation in secondary prevention programs. Contemporary approaches to CHD secondary prevention may help to overcome this treatment gap. A recent meta-analysis demonstrated that innovative, tele-based CHD secondary prevention programs may transcend some of the barriers to participation in traditional rehabilitation programs, and they are effective in improving behavioural and clinical outcomes for cardiac patients [16]. Further, telephone-delivered therapy has proven effective for patients with depression [17] and more recently, for those with co-morbid depression following a cardiac event. For example, a tele-health, nurse-delivered, collaborative care intervention for coronary artery bypass graft surgery patients suffering from depression significantly improved depression outcomes, mental health components of HRQOL and disease specific physical functioning [18].

Psychological based therapies [19,20], pharmacologic approaches (namely Selective Serotonin Reuptake Inhibitors)[21], and composite approaches to treatment [22,23] have all demonstrated improvements in depression for CHD patients, especially for those with recurrent depression [24]. While pharmacologic and psychological approaches have yielded comparable effect sizes in reducing depression [25], Cognitive Behaviour Therapy (CBT) has been shown to be particularly favourable for improving depression outcomes for cardiac patients, with an American Heart Association report endorsing its use [26]. Evidence from a number of well designed trials also demonstrate its effectiveness in reducing depression in cardiac patients when compared with other approaches [19]. For example, compared to usual care (UC), Freedland and colleagues (2007) demonstrated that CBT displayed greater and more durable effects than the other approaches [19]. However, relatively little is known about its effectiveness under 'real world' delivery conditions, particularly using a tele-based approach.

The feasibility of combining a tele-health, depression management program using CBT with a CHD secondary prevention program for ACS patients is yet to be established in the 'real world' setting. The effects of such a program could go beyond treating depression to improve all aspects of HRQOL and CHD risk factors, and demonstrate significant economic advantages over more traditional modes of delivery. This paper presents the study protocol for a randomised, multi-centre, feasibility trial of a tele-health intervention for ACS patients with depression ('MoodCare'). We hypothesise that the trial will demonstrate the feasibility of the MoodCare intervention through improving key depression and HRQOL outcomes at 6 months, with increased participant satisfaction, and will be cost-effective compared with UC.

## Methods

We are currently enrolling 100 ACS patients in a prospective, multi-centre, feasibility trial with patients randomised to either the intervention or UC control group. Participants in both groups complete assessments at baseline (Time 1), post-intervention or 6 months follow-up (Time 2), as well as at 12 months (Time 3), and 24 months (Time 4) for longer term effects.

### Study Aims

#### Primary Aim

To investigate the feasibility of a telephone-delivered, depression management and CHD secondary prevention intervention for ACS patients over 6 months. Prospective outcomes include: changes in depression using the Cardiac Depression Scale (CDS) and changes in HRQOL using the Short Form-12 (SF-12), cost-effectiveness and participant acceptability compared with UC.

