#### Intervention Implementation and Acceptability

To assess program implementation, participant acceptability is measured by a self-administered questionnaire at Time 2. Self-administered satisfaction questions include: 'how would you rate the MoodCare Participant Handbook' (*excellent *to *poor*); 'how would you rate your sessions with the Counsellor (*very useful *to *not useful at all)*; 'did you get what you expected from the program' (*yes definitely *to *no definitely not)*; 'to what extent has the program met your needs' (*almost all of my needs have been met *to *none of my needs have been met); *'has the program helped you to deal more effectively with your health issues' (*yes it helped a great deal *to *no it seemed to make things worse)*; 'in general how satisfied are you with the program (*very satisfied *to *very dissatisfied)*; 'were you satisfied with the length of the counselling sessions' (*yes, no)*; 'were you satisfied with the number of counselling sessions' (*yes, no)*; and 'were you satisfied with the length of the program overall' (*yes, no)*. Participants are also asked to highlight the strengths and weaknesses of the program in two open-ended questions. Participant adherence to the intervention is assessed by: the proportion of sessions completed during the intervention period; the topics covered in each session; and the total length (minutes) of intervention exposure during the six month period.

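### The primary aim compares participant acceptability with usual care, but every listed acceptability item concerns MoodCare components that controls do not receive

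*Protocol article*

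**What the plan says.** The Primary Aim (Protocol article, Study Aims) ends its list of outcomes with "cost-effectiveness and participant acceptability compared with UC". The hypothesis at the end of the Background expects the program to succeed "with increased participant satisfaction, and will be cost-effective compared with UC".

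Measurement is described in one place, Intervention Implementation and Acceptability: "participant acceptability is measured by a self-administered questionnaire at Time 2". The listed items include "how would you rate the MoodCare Participant Handbook", "how would you rate your sessions with the Counsellor", "did you get what you expected from the program" and "in general how satisfied are you with the program". Two open-ended questions and three measures of adherence follow.

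Under Study conditions, the handbook and telephone sessions go to the intervention arm. Controls continue with usual medical care. Both arms get an education pamphlet and a newsletter.

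**The concern.** The aim and the hypothesis both state acceptability as a contrast: one names usual care, and the other says satisfaction will be increased. The instrument asks about things that exist in one arm only. A control participant has no handbook to rate and no counsellor sessions to judge.

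At stake is one named element of the primary aim. Randomisation gives no protection to an outcome measured in one arm. If intervention participants rate the program well, a report that follows the hypothesis could present this as increased satisfaction relative to usual care, although nothing comparable had been measured in controls.

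**Working it through.** The plan gives no figure for acceptability, so the check is a classification. Each measure under Intervention Implementation and Acceptability is set against what controls receive under Study conditions.

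| Measures | Number | Subject | Applies to controls |
|---|---|---|---|
| Closed item on the handbook | 1 | MoodCare handbook | 0 |
| Closed items on the counsellor and on session length and number | 3 | Counselling sessions | 0 |
| Closed items on expectations, needs, help with health issues, general satisfaction and overall length | 5 | The program | 0 |
| Open-ended questions | 2 | The program | 0 |
| Adherence: share of sessions completed, topics, minutes | 3 | Counselling sessions | 0 |
| **Total** | **14** | | **0** |

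The closed items sum to 1 + 3 + 5 = 9, and all measures to 9 + 2 + 3 = 14. No listed item asks about the pamphlet, the newsletter or usual care. If controls were sent the five closed items that refer only to the program, their answers would concern something other than MoodCare, so the two arms would not be rating the same thing.

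Next, whether another part of the article supplies what is missing:

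- Table 1 lists no satisfaction or acceptability measure for either arm.
- Data Analyses plans between-arm comparisons for the Cardiac Depression Scale (CDS) and quality of life only.
- The questionnaire is given at Time 2 only, so increased cannot mean a rise from an earlier rating by the same person.

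The intervention-arm rating can still be estimated usefully. The number of respondents and the satisfied proportion are assumptions here. With 80% satisfied, the 95% half-width is 1.96 × √(0.8 × 0.2 / n):

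- n = 40 (50 randomised per arm less 20% attrition): 1.96 × √(0.16/40) = 0.124, about 12 percentage points.
- n = 50 (the number per arm that Sample Size Calculations requires to complete): 1.96 × √(0.16/50) = 0.111, about 11 percentage points.

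These figures describe the precision of a one-arm estimate. They do not measure the mismatch.

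**The case against.** The strongest defence is that the operative methods never plan an acceptability comparison. The Abstract separates comparing CDS and SF-12 between arms from assessing feasibility through acceptability. The acceptability section is framed as program implementation. The article names CDS and SF-12 as the two primary outcomes, and acceptability is not one of them. On this view the closing words of the aim trail loosely after a list. This stands in part: it shows that the investigators probably intended a descriptive outcome, and that no planned analysis or power figure depends on the contrast. It does not remove the mismatch, because a phrase that covers the whole list still covers acceptability, and the hypothesis independently needs a reference for increased.

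A second defence is that the article introduces the questions as including those shown, and an article condenses its instruments. This stands as a limit. An unlisted item that controls could answer cannot be excluded, so the point concerns every listed item. It does not show that the control arm has no satisfaction data at all.

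A reader might also infer from "will demonstrate the feasibility of the MoodCare intervention through improving key depression and HRQOL outcomes at 6 months" that feasibility otherwise rests on efficacy alone, so that an effective program with poor uptake would be declared feasible. The documents do not support that. The data collection section says feasibility will be determined by the measures that follow, and these include cost-effectiveness, acceptability, adherence, and the Reach, Adoption and Maintenance elements of RE-AIM. No rule makes efficacy decisive. Nor do the screening, recruitment and attrition figures serve as ready feasibility criteria. They are planning assumptions, and turning them into thresholds would be a preference rather than a correction.

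**Conclusion.** The point holds as a mismatch between a stated aim and its described instrument. None of the 14 described measures gives a control-arm value, so the plan as written yields no between-arm estimate of acceptability. Intervention-arm ratings alone cannot support a claim of increased satisfaction versus usual care. This is not a detail left to an analysis plan, since the article states both the comparative aim and the items, and no analysis method can create the missing control values.

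The conclusion assumes that the listed items represent the questionnaire. It reaches only the acceptability element of the primary aim. The CDS, SF-12 and cost-effectiveness comparisons and the sample size are untouched. It should be corrected because the wording invites a claim that the data could not bear.

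**What to change.** Choose one of two routes.

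1. **Descriptive outcome.** In the Primary Aim, confine the comparison with usual care to CDS, SF-12 and cost-effectiveness, and state acceptability separately as an intervention-arm outcome reported with a 95% confidence interval. In the Background hypothesis, delete the word increased. The cost is rewording and a more modest aim.
2. **Comparative outcome.** If a contrast is wanted, add one generic question on satisfaction with care received to both arms' Time 2 postal survey, which Table 1 already schedules. Keep the program-specific items for the intervention arm. The cost is one extra question. Recruitment began in December 2009, so anyone already past Time 2 when it is added would have no answer, and the report should state how many are affected in each arm.

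The first route fits the methods as they stand.

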#### Secondary Aims

(i) To investigate the longer term feasibility of implementing the MoodCare program at 12 and 24 months follow-up.

### Study Sample

#### Eligibility Criteria

Eligibility criteria includes: a clinical diagnosis consistent with that of ACS (MI [STEMI or non STEMI] or unstable angina confirmed by angiogram), aged 21-85 years, fluency in English, availability via the telephone for the duration of the study, and a Patient Health Questionnaire (PHQ9) score of 5-19. Patients are excluded if they are: participating in regular psychological therapy with a mental health professional at the time of admission for ACS, diagnosed with a psychiatric condition which may impact on involvement (including bipolar disorder, psychotic illness of any type, dementia, acute suicidality, severe personality disorder), cognitively impaired impacting on their ability to participate in the study, diagnosed with a terminal illness, or unable to participate in a tele-based unsupervised mood and lifestyle intervention as confirmed by the treating clinician.

#### Sample Recruitment Procedures

We are screening more than 1600 patients over approximately 15 months from six metropolitan hospitals in Victoria and Queensland, Australia. Recruitment commenced in December 2009. All consenting patients are assessed for depression prior to hospital discharge using a psychometrically robust and valid instrument (PHQ9) [27]. Patients with a PHQ9 score of 5-19 are eligible to participate. This scoring range was selected due to its high sensitivity and specificity, as opposed to the commonly used cut off of ≥ 10, which has comparable specificity (92% and 90%, respectively), but poorer sensitivity (39% and 54%, respectively) [28]. Patients with a PHQ9 score <5 are provided with relevant feedback, reassurance and advice. Any persons indicating suicidal thoughts on PHQ9 and/or those with severe depression, as indicated by PHQ9 scores of 20-27, are referred for further assessment by a mental health professional and possible study exclusion. Algorithms are in place for patients assigned to the intervention whose condition deteriorates throughout the program, and who are no longer eligible or lost to follow up throughout the course of the trial.

Eligible participants are subsequently contacted by the research team via telephone within 1-2 weeks of discharge to complete Time 1 data collection. This includes a secondary assessment of depression in order to determine severity. Participants initially respond to a two item screening tool which has a positive endorsement of the first two PHQ items [28], before undertaking the full Composite International Diagnostic Interview (CIDI) assessment.

#### Sample Size Calculations

Anticipating an attrition rate of 20% throughout the study, n = 125 participants are required to achieve a final sample size of n = 100. Sample size analysis indicated that 50 subjects per group (intervention and control) or a total of 100 are required to complete the study in order to detect an absolute intervention effect with 80% power and type I error of 5% (two-tailed). Sample size was calculated based on an overall difference between participants in the intervention and control groups in the primary outcome measure of depression scores at 6 months, where a sample size of n = 100 was sufficient to detect a difference in mean CDS scores of 6.8, assuming a between-patient SD of 12 [29]. Assuming persistence of effect to 12 months and a conservative correlation of 0.30 between baseline, 6 months and 12 months CDS scores, a pooled analysis at 6 and 12 months will have 80% power to detect a difference of 5.1 units (a change score of 5 on the CDS is considered clinically meaningful).

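### The protocol gives two sample sizes: 125 participants needed so that 100 complete, but 100 enrolled and randomised

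*Protocol article*

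**What the plan says.** Three places in the protocol article give the number of participants.

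- **Sample Size Calculations.** The text begins "Anticipating an attrition rate of 20% throughout the study" and continues "n = 125 participants are required to achieve a final sample size of n = 100". It then says that "50 subjects per group (intervention and control) or a total of 100 are required to complete the study", "with 80% power and type I error of 5% (two-tailed"), and that this number is "sufficient to detect a difference in mean CDS scores of 6.8, assuming a between-patient SD of 12". A pooled 6- and 12-month analysis, with a correlation of 0.30 among the baseline, 6-month and 12-month scores, is said to have 80% power for 5.1 units. A change of 5 on the CDS is called clinically meaningful.
- **Abstract, Methods.** "One hundred eligible participants are to be randomised to an intervention or a usual medical care control group (50 per group").
- **Methods, opening paragraph.** "We are currently enrolling 100 ACS patients in a prospective, multi-centre, feasibility trial".

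Four other statements bear on the reading. Study Integrity places randomisation after Time 1 data collection. Study conditions says that the letter sent to primary care on enrolment reports the group to which the patient was randomised. The outcomes section makes 6 months the primary assessment point, while follow-up runs to 24 months. Data Analyses uses the baseline value as a covariate where relevant, and linear mixed models for the pooled analyses.

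**The concern.** In the sample size section, 100 is the number left at the end and 125 the number needed at the start. In the abstract and the Methods opening, 100 is the number at the start. With any attrition, both cannot be true, and no statement plans to enrol or randomise 125.

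Recruitment was under way when the article was written, so the figure determines when enrolment stops. Stopping at 100 gives up the attrition allowance that the plan itself judged necessary. The 6.8 and 5.1 detectable differences, each quoted at 80% power, are tied to 50 completers per group. The pooled 5.1 is also the only detectable difference close to the 5-point change that the plan calls meaningful.

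**Working it through.** **Inputs, all from Sample Size Calculations:** two-sided alpha 0.05; power 80%; difference 6.8; SD 12; 50 completers per group; attrition 20%; correlation r = 0.30 for the pooled analysis.

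**Step 1: reproduce the plan's figures.**

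- Power is that of a two-sample t-test (noncentral t) with n per group, 2n − 2 degrees of freedom and noncentrality δ / (SD × √(2/n)). For n = 50, 6.8 / (12 × √(2/50)) = 6.8 / 2.40 = 2.83. Power is 80.1%, and the difference detectable at 80% power is 6.79, matching the stated 6.8.
- Attrition: 100 / (1 − 0.20) = 125, as stated.
- Pooled: for the baseline-adjusted mean of two follow-up scores, the variance factor is (1 + r)/2 − r² = 0.65 − 0.09 = 0.56, so the SD is 12 × √0.56 = 8.98. At 50 per group the detectable difference is 5.08, matching the stated 5.1.

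All three figures reproduce, so the calculation itself contains no error.

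**Step 2: test whether 125 could be a count before randomisation.** The attrition is described as occurring throughout the study, and the 100 "are required to complete the study in order to detect an absolute intervention effect with 80% power". Randomisation follows the baseline assessment, so losses at 6, 12 and 24 months all fall on randomised patients. Enrolment is itself given as 100, and the primary care letter ties enrolment to randomisation. That reading does not remove the conflict.

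**Step 3: consequences if 100 are randomised.** With the full 20% loss, 100 × 0.80 = 80 remain, or 40 per group. With baseline adjustment at r = 0.30, the SD for a single time point is 12 × √(1 − 0.09) = 11.45. The plan gives no attrition rate at 6 months, so 10% (45 per group) and 8% (46 per group) are my assumptions, to show the range.

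| Completers per group | Power for 6.8, unadjusted | Power for 6.8, baseline-adjusted |
|---|---|---|
| 50 (as planned) | 80.1% | 83.7% |
| 46 (8% lost, assumed) | 76.7% | 80.5% |
| 45 (10% lost, assumed) | 75.8% | 79.6% |
| 40 (full 20% lost) | 70.6% | 74.7% |

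At 40 per group the difference detectable at 80% power is 7.61 unadjusted and 7.26 adjusted. For the pooled analysis at 40 per group it is 5.70, and power for 5.1 is 70.8%.

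**Step 4: consequences if 125 are randomised.** Then 125 × 0.80 = 100 complete, 50 per group, and the plan's figures stand.

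**The case against.** A reader might infer that the trial does not deliver its stated 80% power, or that none of its stated power properties survive. The documents do not support either statement, for three reasons.

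1. *The operative target is not settled.* Sample Size Calculations is the only section that derives the number, and it asks for 125. The abstract and the Methods opening may simply quote the completer target loosely. In that case the power is as stated.
2. *The 71% is a worst case.* It applies a whole-study loss, with follow-up to 24 months, in full at the 6-month primary assessment. It also ignores the baseline covariate. With adjustment at the plan's own r = 0.30 and 8–10% lost by 6 months, 100 randomised gives about 80%. The 5.7 likewise assumes that every lost patient contributes neither a 6- nor a 12-month score, whereas the mixed model uses partial data.
3. *This is a feasibility trial reporting estimates with 95% confidence intervals.* A shortfall in numbers biases no estimate and leaves the type I error untouched.

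The first two reasons stand, and they limit the claim to an inconsistency with a conditional cost. The third is fair as to gravity but does not excuse the conflict: the article makes a formal power claim, hypothesises improvement in depression and quality of life at 6 months, and says in its Discussion that efficacy will be evaluated. Nor is this detail that an article leaves to a fuller document, since both numbers are printed and they disagree.

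**Conclusion.** The sample size is internally inconsistent. The figure of 100 serves as the number that must complete in one section and as the number enrolled or randomised in two others. This holds whatever attrition is assumed.

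The cost depends on which target governs. Under 125 there is no loss of power. Under 100, the plan's own unadjusted calculation falls short of 80% for 6.8: by about 9 percentage points with the full 20% loss, and by about 3 to 4 points with an assumed 8–10% loss by 6 months. With baseline adjustment the shortfall is about 5 points at worst and essentially nil at 8–10% loss. The pooled detectable difference would be at most 5.7 rather than 5.1. These results assume SD 12, equal groups, equal loss in both groups and, for the adjusted figures, r = 0.30.

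**What to change.** State one randomisation target in the abstract, the Methods opening and Sample Size Calculations.

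- **If 125 was intended:** correct the abstract and the Methods opening to 125 randomised, about 62–63 per group. The sample size section can stay. If recruitment is already planned to 125, this is a wording change only; if it was to stop at 100, it means 25 more participants.
- **If 100 is the number to be randomised:** keep it, and replace the 125 and the associated power statement with the expected completers, power and detectable differences. Name the attrition assumed at 6 months, separately from the whole-study 20%, and say whether the figures include baseline adjustment. Under the full 20% loss the text would give about 80 completers, 71% power for 6.8 and a detectable difference of 7.6 (75% and 7.3 adjusted), and 5.7 for the pooled analysis. This costs wording only.

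The choice should be recorded before recruitment closes.
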